### **Trial course**

The trial course is outlined in Figure 1. Patients are admitted to the Department of Surgery, Herlev Hospital, with suspected acute appendicitis and a general panel of blood samples are collected. A surgeon from the department will either plan for an acute surgery or keep patients for further observation. The primary investigator of the trial approaches these otherwise healthy patients to give information about the trial. Thereby we ensure the patient has plenty of time for consideration in this setting where an acute disease is involved. Patients, who fulfil the inclusion criteria and present none of the exclusion criteria, apart from those criteria that can only be clarified at surgery, are enrolled in the trial after informed consent. Baseline characteristics of the enrolled patients will be noted in the case report form (CRF). A note of the patient's enrolment in the trial will be added to the patient's medical record, so the standard intravenous antibiotics are not administered. The patients are included in the trial during the surgery when the operating surgeon or a supervisor visually confirms the diagnosis of uncomplicated appendicitis. Patients that fulfil any exclusion criteria are excluded from the trial and will receive treatment and antibiotics according to standard clinical practice. Included patients will have their appendixes removed laparoscopically according to standard clinical practice. When the appendix has been removed from the abdominal cavity through an Endobag and haemostasis has been secured, a minimum of 500 ml of saline will be used for irrigation of the abdominal cavity. Hereafter the trial treatment will be instilled into the abdominal cavity under the supervision of the trial investigator to ensure full compliance. The patients will have vital signs measured at baseline, 5 minutes, 10 minutes, 15 minutes, 4 hours and 12 hours after the trial treatment during

their hospital admission. These values will be noted in the CRF. Participants will be peri- and postoperatively monitored according to standard practice.

Postoperatively, the general panel of blood samples will be repeated 4 hours after the trial treatment, which differs from standard clinical practice. Side effects are evaluated through the following procedures. The primary investigator will perform an objective examination of the participant and ask if any changes have risen 12 hours after the trial treatment has been administered. This will be noted in the CRF. When the patient has a “Postanesthetic Recovery Score for Patients Having Anesthesia on Ambulatory Basis” (PARSAP)  $\geq 18$  and is informed about the procedure the patient will be discharged according to clinical practice. PARSAP is found in Supplements, Table 2.

Ten days after the trial treatment has been administered side effects will be evaluated again. The primary investigator will meet with the participant to perform an objective examination and ask if any changes have risen since the surgery. This will be noted in the CRF.

A follow-up of the participants will be performed 30 days after the surgery through medical records and contact to the participant by telephone, which will be noted in the CRF.

[figure not shown]

*Figure 1. The trial course for participants in the main trial: Safety. An outline (black text) of the normal course of admission for appendicitis is seen at the bottom. The timespan for enrolment and inclusion are marked in grey boxes. All investigations related to the trial are shown in blue text and in the blue boxes. These include blood samples, vital signs (pulse, blood pressure, temperature, frequency of respiration, and SAT), and objective examinations combined with questions about any changes to evaluate side effects. Finally, a follow-up will be conducted 30 days after the surgery. The measurement of vital signs during the surgery will be performed at baseline, 5, 10 and 15 minutes after the trial treatment has been administered.*

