### **Measurements**

Primary outcome:

- Preoperatively, white blood cell counts at admission (baseline) compared with white blood cell counts 4 hours  $\pm$  30 minutes postoperatively are analysed by Department of Clinical Biochemistry, Herlev Hospital according to their usual standards. The blood samples are destroyed after analysis. A toxic effect defined by a drop below the reference range.

Secondary outcomes:

- Preoperative biochemical markers are analysed at admission (baseline) and 4 hours  $\pm$  30 minutes postoperatively by Department of Clinical Biochemistry, Herlev Hospital according to their usual standards. These include a standard panel of blood samples, which are seen in Supplements, Table 3. The blood samples are destroyed after analysis. This requires a total of 20.5 ml blood.
- Vital signs (pulse, blood pressure, temperature, frequency of respiration, and SAT) are measured perioperatively (baseline, 5 minutes, 10 minutes

and 15 minutes after the trial treatment has been administered) and postoperatively (4 and 12 hours  $\pm$  30 minutes after the trial treatment has been administered).

- Length of stay in hours postoperatively.
- Side effects: evaluated through an objective examination and questions about changes 12 hours  $\pm$  30 minutes and 10 days postoperatively  $\pm$  1 day.
- Adverse events: registered from the surgery until 30 days postoperatively through medical records and contact with the participant by telephone.

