### **Side effects of GM-CSF**

GM-CSF has overall been reported well tolerated regardless of route of administration. GM-CSF administered intravenously in an RCT in patients requiring admission to the intensive care unit reported reversible oliguria as the only side effect. A pharmacokinetic study of escalating doses (0.3, 1, 3, 10, 15, and 20 µg/kg/day) in patients with advanced malignancy and/or neutropenia reported the following most common adverse clinical effects: 71% bone pain, 62% lethargy/malaise, 38% rash and/or pruritus, 38% first dose reaction, 29% fever, 24% fever and rigors, 14% weight dose gain, 10% marginal keratitis, 10% nasal congestion, and 10% pericardial pain. Adverse effects such as fever, pericarditis, and liver abnormalities were not seen in

patients receiving  $<10 \mu\text{g/kg}$ . Also transient leukopenia was seen after intravenous administration. The first dose reaction is characterised by either symptomatic hypotension, hypoxia or both and at least two other common symptoms (flushing sensation, muscular or bone aches, throbbing lumbar back pain, dyspnoea, nausea and vomiting, rigor or fever, and involuntary leg spasms). This happened within  $60 \pm 40$  minutes after intravenous injection or infusion. Subcutaneous administration in patients with sepsis resulted in no side effects. However, the first dose reaction was associated with high serum concentrations and an intravenous administration route. Another pharmacokinetic study reported bone pain, chills/rigors, dyspnoea, fever, serositis and thrombosis after intravenous administration of escalating doses of GM-CSF of 1, 2, 4, or  $8 \mu\text{g/kg/day}$ . One pharmacokinetic study did not report on adverse effects.

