### **Side effects of the instilled volume**

After the intraperitoneal administration of drugs, a volume of 500 ml will remain as an instillation in the abdominal cavity, which will then be gradually absorbed. In a recent RCT, 500 ml of saline were instilled as an intervention after laparoscopic cholecystectomy to investigate effects on pain, recovery and quality of life. The control group did not receive any fluid instillation. There was no difference in pain, recovery, or quality of life between the two groups. The only significant outcome was increased nausea one hour after surgery in the intervention group. However, there was no difference at the subsequent time points at four hours, one day, and seven days postoperatively. No other adverse effects were reported. Therefore we expect the planned volume of 500 ml to be without side effects for the patients.

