## Summary

**Background:** In secondary peritonitis, bacteria that have escaped from abdominal organs cause an infection in the abdominal cavity. Peritonitis can have long-term consequences for the patients. The severity of the disease depends on the extent of inflammation. Current treatment practice is surgical intervention (source control) in combination with the administration of intravenous antibiotics. We wish to administer two antimicrobial agents: fosfomycin and metronidazole, together with granulocyte-macrophage colony-stimulating factor (GM-CSF), which stimulates the function of macrophages. The surgical intervention is kept. The trial drugs are administered at the site of the disease: intraperitoneal administration. Thereby the abdominal cavity receives highest concentration of the drugs. Furthermore, in addition to the antimicrobial treatment, the patient's local immune defence is stimulated by GM-CSF.

This pilot trial will be conducted in otherwise healthy patients suffering from uncomplicated appendicitis. The administration of the trial treatment demands an intra-abdominal access, which is routinely established during surgery. The trial will consist a main trial: Safety and a sub-trial: Pharmacokinetics that involve and recruit from the same trial population.

**Main trial: Safety:** The primary objective is to investigate if intraperitoneal administration of fosfomycin, metronidazole, and GM-CSF is safe, on the basis of white blood cell counts four hours after the surgery. Secondary objectives are measurements of vital signs at baseline, 5, 10 and 15 minutes and again 4 and 12 hours after administration of the trial treatment, length of stay and side effects evaluated by an objective examination and questions about changes 12 hours and 10 days after administration of the trial treatment. A follow-up is conducted 30 days after the surgery. Fourteen otherwise healthy males  $\geq 18$  years diagnosed with uncomplicated appendicitis are needed to complete the main trial.

**Sub trial: Pharmacokinetics:** The primary objective is to investigate the plasma concentrations of fosfomycin after intraperitoneal administration over time. Secondary objectives are investigations of metronidazole concentrations after intraperitoneal administration over time and microbiologic investigations of

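### The recorded vital signs leave 15 minutes to 4 hours uncovered, so this safety outcome cannot by itself show that early effects the protocol describes were absent

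*Protocol*

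**What the plan says.** Vital signs are a named secondary outcome of the main safety trial. Their schedule is given three times, consistently.

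- Trial course: "The patients will have vital signs measured at baseline, 5 minutes, 10 minutes, 15 minutes, 4 hours and 12 hours after the trial treatment", followed by "These values will be noted in the CRF".
- Measurements: the signs "are measured perioperatively (baseline, 5 minutes, 10 minutes" "and 15 minutes after the trial treatment has been administered) and postoperatively (4 and 12 hours", with a leeway of ±30 minutes printed after the two postoperative times.
- Summary: "measurements of vital signs at baseline, 5, 10 and 15 minutes and again 4 and 12 hours after administration of the trial treatment".

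The section on side effects of GM-CSF describes the event that these signs are well placed to detect: "The first dose reaction is characterised by either symptomatic hypotension, hypoxia or both and at least two other common symptoms". It puts the timing at 60 ± 40 "minutes after intravenous injection or infusion". The same section links the reaction to the intravenous route and to high serum concentrations. It adds that a study using both routes saw it only after intravenous dosing.

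On the fluid itself, the section on the instilled volume reports from a randomised trial of 500 ml saline: "The only significant outcome was increased nausea one hour after surgery in the intervention group". That difference had gone by four hours.

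The first scheduled question about symptoms is at 12 hours ± 30 minutes. Trial course also says that standard peri- and postoperative monitoring applies. It gives no times for this monitoring and does not say that those readings enter the CRF.

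**The concern.** The aim of the trial is safety, and the three drugs have, to the sponsor's knowledge, not been given together before (The combination of the drugs). Blood pressure and saturation are the two signs that define the first-dose reaction. Both are recorded very early and then not again for almost four hours. The one adverse effect that the protocol cites for the instilled volume also falls in the unrecorded period.

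A report based on these data could say that vital signs showed no effect when no trial reading had been scheduled in the interval of interest. Readings that are not specified in advance may not be recoverable afterwards at comparable times for all participants.

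**Working it through.** **Inputs**

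- Recorded times after treatment (Trial course, Measurements, Summary): 0, 5, 10, 15, 240 and 720 minutes.
- Leeway at 4 and 12 hours (Measurements): ±30 minutes.
- First-dose reaction after intravenous GM-CSF (Side effects of GM-CSF): 60 ± 40 minutes.
- Excess nausea (Side effects of the instilled volume): present 1 hour after surgery, no difference at 4 hours.
- Pharmacokinetic blood samples (sub-trial, Trial course): ½, 1 and 2 hours, in 8 of the 14 participants, with no vital signs attached.

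**Step 1: the cited interval.** 60 − 40 = 20 and 60 + 40 = 100, so 20 to 100 minutes. The protocol does not say whether ±40 is a standard deviation or a range, so these are not hard limits.

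**Step 2: recorded times inside it.** None of 0, 5, 10, 15, 240 and 720 lies between 20 and 100.

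**Step 3: length of the gap.** Nominal: 240 − 15 = 225 minutes. The earliest permitted 4-hour reading is at 240 − 30 = 210 minutes and the latest at 240 + 30 = 270. The gap therefore runs from 210 − 15 = 195 to 270 − 15 = 255 minutes. The leeway does not bring a reading near 100 minutes.

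**Step 4: nausea at 1 hour.** This time is counted from the end of surgery, not from instillation. For it to fall after the earliest 4-hour reading, surgery would have to continue for more than 210 − 60 = 150 minutes after instillation. Instillation follows removal of the appendix, haemostasis and irrigation, so the 1-hour point very probably lies in the gap. The symptom enquiry at 12 hours comes 8 hours after the cited difference was no longer seen (12 − 4 = 8).

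**Step 5: effect of adding ½, 1 and 2 hours.** The times become 0, 5, 10, 15, 30, 60, 120, 240 and 720 minutes. Two of them (30 and 60) lie within 20 to 100. The longest interval before the 4-hour reading falls from 225 to 240 − 120 = 120 minutes.

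**Step 6: the baseline.** Measurements calls the readings from baseline to 15 minutes perioperative, and the legend of Figure 1 places them during surgery. The 4- and 12-hour readings are postoperative. The protocol states no change-from-baseline analysis for vital signs, so this matters only if such changes are reported.

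**The case against.** The strongest reply concerns the route. The 60 ± 40 minutes belongs to intravenous dosing, and the protocol gives no onset time for intraperitoneal dosing. Of the two intraperitoneal studies cited, the one that used both routes saw no first-dose reaction intraperitoneally. The other, at 68 µg/day, reported only a passing flu-like syndrome. The dose here is a single 50 µg, which the protocol calls low. This stands: a reader might infer that the protocol itself predicts the reaction in the unrecorded window for this trial, and it does not.

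Nor can a risk be read from the intravenous figures. If ±40 were the standard deviation of a normal onset time, Φ((15 − 60)/40) = Φ(−1.125) = 0.13. About 87% of reactions would then start after 15 minutes, or about 93% with the distribution truncated at zero. The intravenous escalation study reported the reaction in 38% of patients. Those percentages describe another route, doses up to 20 µg/kg/day, and patients with advanced malignancy and/or neutropenia. For assumed body weights of 60 to 100 kg, 50 µg is 50/60 = 0.83 to 50/100 = 0.50 µg/kg. None of these percentages estimates risk here.

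It is also fair to say that patients are not unobserved. Standard monitoring continues, and adverse events are registered from surgery to day 30, in part from medical records. The reaction is by definition symptomatic, so it could surface that way. The discharge score (Supplements, Table 2) covers blood pressure, saturation and nausea, but it has no fixed time and is not stated to enter the CRF. A reader might infer that nothing would be detected; the documents do not support that.

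What these replies leave untouched is narrower. An expectation drawn from other patients given GM-CSF without these antibiotics is not a measurement in this trial. The outcome as scheduled does not supply that measurement.

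**Conclusion.** The point holds in a limited form. The three statements of the schedule agree, and followed exactly they leave nominally 225 minutes without a scheduled vital sign. That gap covers all of the 20 to 100 minutes cited for the reaction after intravenous GM-CSF and, very probably, the 1-hour nausea finding. The recorded secondary outcome therefore cannot by itself document that either effect was absent.

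The conclusion assumes only that readings from standard monitoring are not otherwise entered as trial data, since the protocol does not say that they are. It does not assume that the reaction is likely after intraperitoneal dosing.

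The primary outcome, the white cell count at 4 hours, is unaffected. The trial is an uncontrolled pilot of 14 with no power calculation, and vital signs are one of several secondary outcomes. This is a worthwhile improvement to data capture, not a condition for the trial to be sound.

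A reader might also infer that the 4- and 12-hour results are confounded by anaesthesia. That would follow only from an analysis of change against the intraoperative baseline, which the protocol does not specify.

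**What to change.** - For all 14 participants, add CRF fields at about ½, 1 and 2 hours after instillation for blood pressure, pulse and saturation, with a yes/no for nausea. Fill them from the standard postoperative monitoring. The times match existing blood draws for the 8 sub-trial participants. This changes what is recorded, not how patients are managed.
- State in Measurements that these readings belong to the vital-sign outcome, so that the schedule there agrees with the risks described under Side effects.
- If changes at 4 and 12 hours are to be reported, refer them to pre-anaesthetic values and keep the intraoperative baseline for the 5- to 15-minute readings. The discharge score already needs a pre-anaesthetic blood pressure.
- If the fields are not added, say in the report that vital signs were not recorded for the trial between 15 minutes and 4 hours.

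**Cost:** a little more data entry. The protocol gives no times for standard monitoring, so whether readings and a nausea note are available at these points must be confirmed first.

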## Side effects

In the following sections the side effects of each drug is described. The side effects of fosfomycin and metronidazole are based on the literature and their respective summary of product characteristics. The summary of product characteristics for fosfomycin and metronidazole will be the reference document for side effects and adverse events. The side effects of GM-CSF are based on the available literature. The reference document for side effects and adverse events of GM-CSF will be the Investigators Brochure. The most common side effects are listed in Table 1 and are experienced by 1-10% of patients receiving the drugs.

| Type of side effect     | Fosfomycin               | Metronidazole  | GM-CSF                  |
|-------------------------|--------------------------|----------------|-------------------------|
| Gastrointestinal | Abdominal pain           | Dry mouth      | Diarrhoea               |
|                         | Vomiting                 | Metal taste    | Nausea                  |
|                         |                          | Nausea         | Vomiting                |
|                         |                          | Oral mucositis |                         |
|                         |                          | Stomatitis     |                         |
| Skin             | Injection site phlebitis |                | Injection site reaction |
|                         |                          |                | Rash                    |
| Other            |                          |                | Anorexia                |
|                         |                          |                | Asthenia                |
|                         |                          |                | Dyspnoea                |
|                         |                          |                | Fatigue                 |
|                         |                          |                | Fever                   |
|                         |                          |                | Musculoskeletal pain    |
|                         |                          |                | Rigors                  |

Table 1. The most common side effect of fosfomycin, metronidazole, and granulocyte-macrophage colony-stimulating factor (GM-CSF).

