### **Reporting of side effects**

The participants will be asked if they have experienced any changes both 12 hours and 10 days after the surgery in combination with an objective examination. This will be documented in the CRF. Further, the patient will be asked if they have experienced any adverse events defined as any unfavourable and unintended sign, symptom, or disease associated with the intraperitoneal treatment, whether or not related to that treatment. A follow-up is conducted 30 days after surgery. This will also be documented in the CRF and will be included in the final report that is sent to the Danish Medicines Authority after the trial.

Serious adverse events (SAE) or serious adverse drug reactions are defined as any untoward medical occurrence that at any dose: results in death, is life-threatening, requires inpatient hospitalization or prolongation of existing hospitalization, results in persistent or significant disability or incapacity, or results in a congenital anomaly or birth defect as defined by ICH-GCP. SAE or serious adverse drug reactions will be reported to the sponsor immediately by the primary investigator.

Unexpected serious adverse reactions (SUSAR) are defined as a SAE or serious adverse drug reactions for which there is a probable causal connection and which is unexpected from the information given in the reference documents (fosfomycin and metronidazole: summary of product characteristics; GM-CSF: investigator's brochure and supplement for intraperitoneal administration). A SUSAR will be reported to the sponsor immediately by the primary investigator, so that it can be reported electronically to the Danish Medicines Authority within 7 days if the occurrence was fatal or life-threatening and within 15 days for all other occurrences. Further, a follow-up will be sent within 8 days. The sponsor will also report any SUSARs to the local Health Research Ethics Committee.

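### Side effects are assessed only after treatment, with no stated symptom baseline and no relatedness step for non-serious events, so symptoms shared with appendicitis or surgery cannot be reliably attributed

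*Protocol*

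**What the plan says.** Side effects are a secondary outcome of the main trial. The Measurements section lists the method: "Side effects: evaluated through an objective examination and questions about changes 12 hours" and 10 days after surgery. The Trial course section gives the procedure. At 12 hours, "The primary investigator will perform an objective examination of the participant" and is to "ask if any changes have risen 12 hours after the trial treatment has been administered". At day 10 the examination is repeated and the investigator is to "ask if any changes have risen since the surgery".

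Before treatment, the protocol states three things:
- An admission blood panel.
- Vital signs, temperature among them, which "are measured perioperatively (baseline, 5 minutes, 10 minutes" and later.
- An unspecified baseline entry: "Baseline characteristics of the enrolled patients will be noted in the case report form (CRF"). Symptoms are not named in it.

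On what to expect, the Side effects section says: "The most common side effects are listed in Table 1 and are experienced by 1-10% of patients receiving the drugs".

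Under Reporting of side effects, participants are asked about adverse events, defined as any unfavourable and unintended sign, "symptom, or disease associated with the intraperitoneal treatment, whether or not related to that treatment". A causal judgement is required only in the SUSAR definition, which applies to serious and unexpected events.

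**The concern.** Asking about a change implies a comparison. Here the comparator is not recorded: it is whatever the participant recalls of his state before treatment, or, at day 10, since the operation. Every participant enters with suspected appendicitis and has had an anaesthetic and an appendectomy by the time he is asked.

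For symptoms common to the disease, the operation and the drugs, the report can err in both directions. Nausea from the anaesthetic may be listed as a side effect. Abdominal pain that the treatment made worse may go unmentioned because it was there already. With no control group described, comparison with each man's own state before treatment is the main discrimination the design offers, and the protocol does not secure the data for it.

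Side effects and adverse events are listed as separate outcomes, but no rule divides them. Under Withdrawal and dropout criteria, stopping the trial depends on effects arising from the treatment, again with no stated way of attributing them.

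**Working it through.** The protocol gives no figure to reproduce here; the 14 participants are not based on a power calculation. The check is therefore what has a pre-treatment value, which terms overlap, and how far attribution could suffer.

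**1. Pre-treatment and post-treatment assessments stated in the main trial**

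| Item | Before treatment | After treatment |
|---|---|---|
| Blood panel | admission | 4 h |
| Vital signs, including temperature | perioperative baseline | 5, 10, 15 min; 4 h; 12 h |
| Trial examination for side effects | none stated | 12 h; day 10 |
| Question about symptoms | none stated | 12 h; day 10 |

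**2. Overlap in Table 1.** The table lists 3 terms for fosfomycin, 5 for metronidazole and 12 for GM-CSF. Nausea and vomiting each appear under two drugs, so the distinct terms number 3 + 5 + 12 − 2 = 18.
- Abdominal pain, nausea, vomiting and anorexia overlap with the entry disease or the operation: 4 of 18.
- Fever would be a fifth, but temperature has a baseline.
- A generous count that adds fever, fatigue, asthenia, diarrhoea and dry mouth reaches 9.

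That these are symptoms of appendicitis is general clinical knowledge; the protocol does not list the symptoms of the disease. The overlap with surgery and fluid is in the protocol itself. It reports more nausea one hour after 500 ml of saline without drug (Side effects of the instilled volume). Its discharge score grades pain, nausea and vomiting after anaesthesia (Table 2).

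**3. Drug-caused cases to expect in 14 men**, from the protocol's 1–10%:
- Term listed for one drug: 14 × 0.01 = 0.14 to 14 × 0.10 = 1.4.
- Nausea or vomiting, listed for two drugs, assuming independence: 1 − 0.99² = 0.0199 and 1 − 0.90² = 0.19, giving 14 × 0.0199 = 0.28 to 14 × 0.19 = 2.66.

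**4. Illustration of attribution.** Let b be the background frequency of a symptom (assumed 10–50%, since the protocol gives none). Let d be the drug effect in men otherwise free of the symptom. Then the observed frequency is q = b + (1 − b)d, and the drug-caused share of reports is (q − b)/q.

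| b | q at d = 10% | Share |
|---|---|---|
| 10% | 0.19 | 0.09/0.19 = 47% |
| 20% | 0.28 | 0.08/0.28 = 29% |
| 30% | 0.37 | 0.07/0.37 = 19% |
| 50% | 0.55 | 0.05/0.55 = 9% |

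At d = 1% the share runs from 0.009/0.109 = 8% (b = 10%) to 0.005/0.505 = 1% (b = 50%). At d = 19% (two drugs) it runs from 0.171/0.271 = 63% to 0.095/0.595 = 16%. For a symptom with almost no background, nearly every report is drug-caused and the difficulty does not arise.

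**5. What an enrolment baseline would remove.** The background b has two parts: symptoms carried over from appendicitis, and symptoms that begin with anaesthesia, surgery or the fluid. Only the first part is already present at enrolment. The protocol gives no split, so step 4 describes the whole attribution problem and not the gain from the fix.

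**6. The adverse-event definition.** Its phrase can mean association in time regardless of cause, which is the usual sense. It can also be read as requiring a link to the treatment and then waiving it. The instruction to record regardless of cause is clear enough; the wording is ambiguous.

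**The case against.** A reader might infer that drug effects cannot be told from the entry disease at all. The protocol does not support that. Most of the 18 terms do not overlap, and metal taste, stomatitis, oral mucositis and rash are little affected. Temperature, blood pressure, saturation and laboratory values have baselines. The open question is accompanied by an examination by the investigator, nothing is scored from the question alone, and nowhere does the protocol say that every reported change counts as a drug effect. Nor is a causal judgement wholly missing, since the SUSAR definition requires one.

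A reader might also set an assumed rate of postoperative nausea against the 1–10% in the protocol and quote a large ratio of noise to signal. The documents supply no such background rate, and nausea is listed for two drugs, which raises the expected signal. More important, nausea caused by the anaesthetic is new since enrolment, so a baseline checklist would not remove it. Such a ratio measures the lack of a control group, not the lack of a symptom record.

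Finally, the CRF is not shown. Its baseline page may contain symptoms, grades or relatedness fields. The record is therefore not specified; it has not been shown to be absent.

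These points narrow the concern but leave its core. An examination at 12 hours with no matching one stated before treatment supplies no baseline. The baseline temperature is itself perioperative. The SUSAR judgement does not reach non-serious reports, where most side effects would fall. And the gap cannot be left to an analysis plan, because symptoms not recorded before treatment cannot be recovered afterwards.

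**Conclusion.** The concern holds in a limited form. No pre-treatment symptom assessment and no relatedness step for non-serious events are stated. For abdominal pain, nausea, vomiting and anorexia (4 of 18 Table 1 terms, up to 9 on a generous count) a reported change therefore has no recorded reference and cannot be reliably attributed to the treatment. Reports may be too many or too few.

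The size of the error cannot be taken from the protocol. On assumed backgrounds of 10–50% and a 10% drug effect, 47% down to 9% of reports would be drug-caused, and an enrolment baseline would repair only the part carried over from appendicitis.

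The primary outcome, the white blood cell count at 4 hours, is untouched. Side effects are a secondary outcome, but a central product of a safety pilot, and the improvement is cheap.

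**What to change.** - Add to the CRF a short checklist of the Table 1 symptoms, graded none, mild, moderate or severe, completed at enrolment, 12 hours and day 10. Keep the open question and the examination.
- Report an item as treatment-emergent only if it is new or worse than at enrolment, and record an investigator judgement of relatedness for each such item.
- Reword the definition under Reporting of side effects so that an adverse event is any untoward occurrence after treatment, whether or not related to it.
- State the limit in the protocol: this removes symptoms carried over from appendicitis, but those caused by anaesthesia, surgery or the instilled volume remain confounded without a control group.

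The cost is one CRF page at contacts the primary investigator already has with each participant. The downside is that prompting may raise the number of mild reports. If the CRF already holds these items, the change is only to say so in the protocol.
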